## Methods/Design

The purpose of this trial is to evaluate whether PCT measurements are able to reduce antibiotic usage in suspected neonatal early-onset sepsis by reducing the duration of antibiotic treatment with unchanged outcome. The study is designed as randomized open controlled international multicenter intervention trial on the efficacy (superiority aspect) and safety (non-inferiority aspect) of PCT guided treatment.

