### Statistical analyses

This trial is designed to exclude a difference in the rates of re-infection or death greater than 2% (non-inferiority aspect of the trial). Assuming a 2% reinfection/death rate in each group, 770 patients are required per arm for a power of 80% at one-sided alpha of 0.025. Based on our data of the study in Lucerne [47], with this number of patients a difference between mean antibiotic therapy durations of 10 hours can be detected at two-sided alpha of 0.05 with a power of 95% (superiority aspect of the trial). To allow for some unevaluable cases 800 per group will be included.

Primary analyses: The two-sided 95% confidence interval for the difference (experimental - control) in re-infection/death rates will be calculated for the total randomized arms and if this difference excludes +2%, non-inferiority is considered to be shown [48]. Comparison of durations of antibiotic therapy will be done using the Mann-Whitney test with stratification by centre. Any patients dying will be considered as the worst outcome in this evaluation and their duration will be set at the highest duration found. All analyses will be done according to the intention-to-treat principle and will be done with stratification by centre. A per-protocol analysis, excluding patients with major protocol violations, will also be done.

Secondary analysis: Exploratory analysis of primary endpoints regarding the relations with and clinical outcomes assessed at T = 24-72 h will be done using logistic regression or Anova. In the Anova the duration's antibiotic treatment will be transformed logarithmically. All tests are two-sided and p = 0.05 is the limit of significance. These analyses will be informal only because it cannot be excluded that the ratings of clinical outcomes at T = 24-72 h are influenced by the PCT results in the PCT-group. In a secondary analysis reinfection/deaths rates will be compared between treatment arms using random effects logistic regression allowing for centre as a random factor.

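### The 95% superiority power is stated for a 10-hour difference in means, but the planned Mann-Whitney test cannot reach it under the article's own category shares

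*Protocol article*

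**What the plan says.** The purpose given under Methods/Design is to see whether PCT measurements are "able to reduce antibiotic usage in suspected neonatal early-onset sepsis by reducing the duration of antibiotic treatment". Under Statistical analyses the sample size comes from the non-inferiority question: "770 patients are required per arm for a power of 80% at one-sided alpha of 0.025". The superiority power is then read off at that size. The text, "Based on our data of the study in Lucerne [47], with this number of patients", states that "a difference between mean antibiotic therapy durations of 10 hours can be detected at two-sided alpha of 0.05 with a power of 95" percent. No standard deviation or distribution is given. The primary analysis is different in kind: "Comparison of durations of antibiotic therapy will be done using the Mann-Whitney test with stratification by centre". For infants who die, "their duration will be set at the highest duration found".

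Two other places bear on this. The Procalcitonin-guided decision making section expects 50% of infants in category 1, 30-35% in category 2, and 15-20% in categories 3 and 4 together. Table 3 gives categories 1 and 2 the same 7-21 days in both arms. PCT-guided stopping applies only to categories 3 and 4, whose standard courses are 5-7 days and 36-72 hours.

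**The concern.** The effect in the power statement is a difference in means, while the test that decides superiority compares ranks. Its power depends on P, the probability that a randomly chosen PCT infant has a shorter course than a randomly chosen standard infant. Nothing in the article links 10 hours to a value of P.

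The link matters because the stopping rule does not shift all durations together. It acts on the infants whose courses are already the shortest. A category 3 infant who stops days earlier contributes many hours to the mean, but in rank passes only other low-risk infants, because the high-risk infants already had longer courses. If such infants are a small minority, a sizeable saving in mean hours leaves P close to one half. A co-primary comparison presented as having 95% power could then be very likely to fail even if the intervention works as intended.

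**Working it through.** **Inputs.** From Statistical analyses: 770 per arm, two-sided alpha 0.05, 10 hours, 95% power. From Procalcitonin-guided decision making: share s of infants in categories 3-4 of 0.15 to 0.20. From Table 3: the duration ranges.

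**1. The article's own figures.** The non-inferiority inputs (2% in each arm, margin 2%, one-sided 0.025, 80% power) reproduce 770 per arm. The 95% cannot be reproduced forwards without an SD. Solving the two-means formula backwards:

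SD = 10 / [(1.960 + 1.645) × √(2/770)] = 54.4 h.

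Sensitivity of the means comparison: SD 50 h gives 97.5% power, 60 h gives 90%, 70 h gives 80%.

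**2. What the Mann-Whitney test needs.** The null standard error of the estimate of P is √[(2n+1)/(12n²)] = √[1541/(12 × 770²)] = 0.01472. For 95% power, P = 0.5 + 3.605 × 0.01472 = 0.553.

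**3. Favourable case: a common normal shift.** P = Φ(10 / (54.4 × √2)) = 0.552, and power is about 94%. For right-skewed (lognormal) durations with the same SD, simulated rank-test power is 99.7% for a pure 10-hour shift and 97% for a 10% reduction in every course.

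**4. The article's own structure.** Let the low-risk share be s in both arms, let low-risk courses lie below high-risk courses (Table 3), and let high-risk courses have the same distribution in both arms. Then:

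- both infants low-risk: probability s², and PCT is shorter with probability at most 1;
- PCT infant low-risk, standard infant high-risk: s(1−s), PCT always shorter;
- the reverse: (1−s)s, PCT never shorter;
- both high-risk: (1−s)², PCT shorter with probability one half.

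The sum is at most s² + s(1−s) + (1−s)²/2 = 0.5 + s²/2.

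| Share s | Maximum P | (P − 0.5)/0.01472 | Maximum power |
|---|---|---|---|
| 0.15 | 0.511 | 0.76 | 12% |
| 0.20 | 0.520 | 1.36 | 27% |
| 0.33 | 0.554 | 3.70 | 96% |

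Exactly 95% needs s = √(2 × 0.053) = 0.33. The bound does not depend on the SD or on how long the high-risk courses are. At 800 per arm the standard error is √[1601/(12 × 800²)] = 0.01444; at s = 0.20 the ratio is 0.02/0.01444 = 1.39, which gives about 28%. The Abstract's statement of more than 80% superiority power is therefore out of reach on these shares too.

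**5. A concrete mixture.** Assume 80% high-risk, 10% category 3 and 10% category 4, Table 3 ranges with uniform durations, high-risk courses of 7-10 days, and every low-risk PCT infant stopped at 24-72 h or at the standard time if earlier. The control SD is 50 h and the mean saving 10.8 h, close to the article's figures. A test of means has 94% power; the Mann-Whitney test has 16%. If high-risk courses instead spread over the full 7-21 days, the rank test stays at 16% and the test of means falls to 32% (control SD 130 h).

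**The case against.** The article does not say which test the 95% was computed for. It points to data from the earlier single-centre study, which are not available here, so the figure cannot be called a miscalculation; it is unsupported for the planned test. A rank test is a reasonable choice for skewed durations with a worst-rank rule for deaths, and under a common shift it loses almost nothing or gains. The 10 hours is presented as a detectable difference at a size already fixed by non-inferiority, not as the expected effect. All of this stands.

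The low power comes from the small share in categories 3-4. If those shares are misstated and low-risk infants are the majority, the rank test has ample power: a simulated 80% share gave 100%, with a much larger mean saving. That is why the shares and the sizing have to be reconciled. The bound also assumes the same share in both arms, as Table 1 intends by making classification independent of PCT. The article admits that ratings may be influenced by PCT results. If 25% of PCT infants and 20% of standard infants were rated low-risk (an assumed shift), the maximum P would be 0.25 + 0.5 × 0.75 × 0.80 = 0.55. Power obtained that way would come from reclassification, and the article does not claim it.

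A reader might also infer that a significant rank test need not mean fewer antibiotic hours. The documents do not support that as a practical risk. One can construct a category 4 pattern with equal means (54 h) and P = 0.61, but the planned test compares whole arms. Placed in full arms, that pattern leads to rejection in only about 3-8% of runs at low-risk shares of 20-50%, and in 45% only in an extreme corner (80% low-risk, 60% of them category 4).

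**Conclusion.** The concern holds as a mismatch between the power statement and the planned test. The 95% for 10 hours is not a property of the centre-stratified Mann-Whitney test. Under a common normal shift the discrepancy is trivial (94% against 95%). Under the article's own expected shares and Table 3 it is large: at most 12% to 27% at 770 per arm, against a stated 95%. This rests on Table 3 being followed, equal category shares in the two arms, and deaths too few or too evenly spread to matter; the calculations are unstratified. It does not show that the rank test is the wrong test, that the original calculation was in error, or that a positive result would mislead about direction.

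**What to change.** Restate the superiority power for the planned Mann-Whitney test. Give the required effect as P (about 0.553 for 95% power at 770 per arm), with the assumed duration distribution and category mix from which it follows. Reconcile the expected shares in the Procalcitonin-guided decision making section with that calculation, and drop the unqualified claim of 95% power for 10 hours. Align the Abstract's power statement with the result.

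Report the centre-stratified difference in mean hours with a bootstrap 95% confidence interval as a supporting estimate. State how deaths enter it, because assigning them the highest duration would make it differ from hours actually used. The Mann-Whitney test can stay as the sole decision rule; no second success condition is needed.

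The cost is a revised power paragraph and one more reported estimate. The restated power may be less favourable than the present one.

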The duration of antibiotic therapy in the standard group is based on the attending physician's assessment of the risk classification during hospitalisation: in category 4 patients, antibiotics are given for 2 - 3 days, in category 3 patients for 5 - 7 days. In the PCT group, if infection is considered to be unlikely or possible, antibiotic therapy is discontinued when two consecutive PCT values are within the normal range (Figure 1 Table 3). Antibiotic therapy can be continued despite fulfilled PCT criteria at the discretion of the attending physician. These diversions from the stopping rules will be reported for further analysis. If infection is proven (category 1) or considered to be probable (category 2) antibiotics are given for 7 - 21 days in both groups.

**Table 3 T3:** Duration of antibiotic therapy

	Standard group	PCT group
**Category 1 and 2**	7 - 21 days	7 - 21 days

**Category 3**	5 - 7 days	at least 24 hours, stop after 2 consecutively negative PCT-values

**Category 4**	36 - 72 hours	at least 24 hours, stop after 2 consecutively negative PCT-values

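### Non-inferiority on safety rests on the intention-to-treat interval alone; the per-protocol analysis has no role in the claim, and it is unclear whether permitted overrides of the PCT stopping rule leave that set

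*Protocol article*

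**What the plan says.** Under Statistical analyses, the protocol article fixes the decision rule for safety in full. The two-sided 95% interval for the difference in re-infection/death rates "will be calculated for the total randomized arms and if this difference excludes +2%, non-inferiority is considered to be shown". The same paragraph adds: "All analyses will be done according to the intention-to-treat principle and will be done with stratification by centre". Of the other analysis set it says only: "A per-protocol analysis, excluding patients with major protocol violations, will also be done". It gives no rule for the case where the two sets disagree.

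Under Procalcitonin-guided decision making, the article allows departures from the stopping rule: "Antibiotic therapy can be continued despite fulfilled PCT criteria at the discretion of the attending physician". It calls these departures diversions from the stopping rules and says they will be reported for further analysis. It sets no limit and no expected frequency, and does not link them to the non-inferiority decision.

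The PCT rule can act only in categories 3 and 4, which the article expects to be 15-20% of infants. Categories 1 and 2 have the same duration rule in both arms. The trial is open.

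The sample size section reads: "Assuming a 2% reinfection/death rate in each group, 770 patients are required per arm" "for a power of 80% at one-sided alpha of 0.025", and then: "To allow for some unevaluable cases 800 per group will be included".

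**The concern.** An infant in the PCT arm whose antibiotics continue after the criteria are met receives treatment close to that of the standard arm. For the superiority question on duration, such infants shrink the observed effect, so intention-to-treat is cautious. For the safety question they also shrink the observed difference, and there a smaller difference favours the claim. The less the rule is followed, the safer it looks.

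The Discussion gives the reason for the non-inferiority design: to show that reduced duration of therapy leaves recurrence and mortality unchanged. Infants whose therapy was not shortened are no evidence for that statement, yet under the present rule they help to pass the test. At stake is a claim that antibiotics can safely be stopped early in newborns with suspected sepsis.

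**Working it through.** **Inputs from the article.** Margin 2 points; event rate 2% in both arms; one-sided alpha 0.025; power 80%; 770 per arm required and 800 recruited; rule-eligible share 15-20%.

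**Assumed.** The override rate f, as a share of rule-eligible PCT infants, because the article gives none; overridden infants carry control-arm risk; the excess under full adherence equals the margin, so 4% v 2%.

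**Step 1: reproduce the plan's figure.** With unpooled variance, n = (1.960 + 0.842)² × 2 × 0.02 × 0.98 / 0.02² = 769.2, rounded up to 770. This matches. At 800 per arm the standard error under equal rates is √(2 × 0.0196/800) = 0.0070, and power is Φ(0.02/0.0070 − 1.96) = 81.5%.

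**Step 2: effect of overrides on the intention-to-treat decision.** The difference becomes d = 0.02 × (1 − f), and P(claim) = Φ((0.02 − d)/SE − 1.96), with SE = √((0.0196 + p(1 − p))/800) and p = 0.02 + d.

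| f (assumed) | d, points | SE | P(claim) | exact binomial, Wald interval |
|---|---|---|---|---|
| 0 | 2.0 | 0.00851 | 2.5% | 3.0% |
| 10% | 1.8 | 0.00838 | 4.3% | 4.9% |
| 20% | 1.6 | 0.00824 | 7.0% | 8.0% |
| 30% | 1.4 | 0.00810 | 11.1% | 12.4% |
| 50% | 1.0 | 0.00780 | 24.9% | 26.4% |

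The last column ignores stratification by centre. Using 770 per arm changes little (6.9% at f = 20%, 10.9% at 30%).

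**Step 3: what the eligible share implies.** If only 15-20% of infants can be treated differently, a 2-point difference across the arm needs an excess of 0.02/0.20 = 10 to 0.02/0.15 = 13.3 points within categories 3 and 4. With 20% overridden, an observed 2-point difference would need 10/0.8 = 12.5 to 13.3/0.8 = 16.7 points.

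**Step 4: does excluding overrides restore the difference?** Take an eligible share of 20%, a 10-point excess there, 2% risk otherwise, and f = 20%. Overridden infants are 0.20 × 0.20 = 4% of the PCT arm. Without them, the PCT rate is (0.80 × 2% + 0.16 × 12%)/0.96 = 3.67%, a difference of 1.67 points, against 1.6 under intention-to-treat and 2.0 under full adherence. With 768 v 800 infants, SE = 0.0084 and P(claim) = Φ(0.0033/0.0084 − 1.96) = 5.9%. Crude exclusion recovers little, because it also thins the categories in which the rule acts. Standardising to the category mix of all randomised infants gives 0.20 × 10 = 2.0 points.

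**Step 5: power of the per-protocol leg at equal 2% rates.** Excluding 5%, 10% or 20% of each arm leaves 760, 720 or 640 per arm and power of 79.5%, 77.4% or 72.4%. Keeping 770 per arm in that set needs 770/0.95 = 811, 770/0.90 = 856 or 770/0.80 = 963 randomised per arm.

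**The case against.** **Intention-to-treat is valid for the strategy as written.** Discretion is part of the PCT arm. For a policy of PCT advice plus physician judgement, the test keeps its nominal 2.5%, apart from a small error of the Wald interval. This stands. The anti-conservatism is relative to the aim in the Discussion, which concerns shortened therapy.

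**Much is already in place.** A per-protocol analysis is planned and overrides are recorded. The detailed definition of the per-protocol set may properly sit in an analysis plan that is not shown. This also stands. What the article itself fixes is that only the randomised arms decide.

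**A reader might infer that overrides, being permitted, cannot be major violations, so the per-protocol set keeps them.** The article does not say so. It calls them diversions from the stopping rules, which leaves either reading open.

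**A reader might also apply override rates of 20-50% to all PCT infants.** On the article's own distribution, 20% of the arm would already be every eligible infant or more. The rates make sense only within categories 3 and 4.

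**Per-protocol exclusion can itself mislead.** Overrides probably select sicker infants, and the same infants cannot readily be identified among controls, where PCT is measured only if blinding of results is feasible. As an illustration with invented whole-arm figures, let 20% be overridden with 4% risk under standard treatment, the rest have 1.5% (overall 0.2 × 4 + 0.8 × 1.5 = 2%), and stopping add 2 points. Intention-to-treat then gives 1.6 points and per-protocol 3.5 − 2.0 = 1.5, with chances of passing of about 7% and 8%. So the per-protocol set can supplement but not replace intention-to-treat.

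**Superiority might fail first under heavy overriding.** Moderate overriding need not do this. If the 10 hours, detectable with 95% power, is the full-adherence effect, normal-approximation power is Φ(3.605 × 0.8 − 1.96) = 82% at f = 20% and Φ(3.605 × 0.7 − 1.96) = 71% at 30%.

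**Conclusion.** The point holds in this form: the decision rule gives the per-protocol analysis no role, and the article leaves open whether permitted overrides are major violations. For the aim of showing that shorter therapy does not change outcome, the rule is anti-conservative. The inflation is from 2.5% to about 4%, 7% or 11% for override rates of 10%, 20% or 30% among eligible infants.

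The direction is secure if overridden infants resemble control. The size is illustrative, since it rests on an assumed override rate, control-arm risk in overridden infants, and a full-adherence excess exactly at the margin. The documents do not support a general statement that the trial's error rate is inflated, because that depends on which question the test is taken to answer. Identical treatment in categories 1 and 2 is a larger and separate source of dilution. This should be changed, but it does not invalidate the design.

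**What to change.** 1. State that non-inferiority is shown only if the two-sided 95% interval excludes +2% in both the intention-to-treat and the per-protocol set.
2. Fix before unblinding whether infants continued on antibiotics despite fulfilled PCT criteria leave the per-protocol set.
3. Adjust the per-protocol comparison for recorded risk category, preferably standardised to the category mix of all randomised infants (step 4 shows why crude exclusion does little). Note the limit: categories are assigned after randomisation, and the article itself concedes that ratings at 24-72 hours may be influenced by PCT results in the PCT group.
4. Report the override rate, and standard-arm departures from the category durations, by arm and category beside the safety result.
5. Reconcile the category 4 standard-arm duration, given as two to three days in the text and 36-72 hours in Table 3. Until then, adherence in that cell cannot be defined.

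**Cost.** The analysis and the data are already planned, so the text change is short, but it is not free of power. The joint rule cannot have more power than its per-protocol leg: 79.5%, 77.4% or 72.4% if 5%, 10% or 20% of each arm is excluded. If only overrides leave the set, the loss is smaller: in the step 4 example, 768 v 800 infants gives Φ(0.02/0.00707 − 1.96) = 80.7%. The stated 80% power should be restated for the joint rule, and the sample size rechecked against the expected exclusions.

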### Laboratory examinations

Complete blood counts and CRP concentrations are obtained in all patients. Serial PCT measurements are performed in all patients of the PCT group and if blinding for the PCT results of the standard group is feasible also in the standard group. Laboratory examinations are stopped by ending of antibiotic therapy. Blood sampling will be limited to normal frequencies already used in daily practice for neonatal care. This means that for this trial blood will collected at time points 0 (moment of inclusion and start point of antibiotic therapy), 24 h (+/- 6 h) after inclusion, between 36 to 72 h after inclusion and then 24-48 hourly until end of antibiotic therapy. One additional sample will be collected in the PCT group 12 h (+/- 6 h) after inclusion. With the exception of the one additional sample in the PCT group, no additional punctures will be done for research purposes.

Procalcitonin will be measured on the automated Kryptor platform, supplied by the firm BRAHMS AG of Hennigsdorf, Germany, via the Roche Elecsys BRAHMS procalcitonin assay. The BRAHMS Kryptor sensitive procalcitonin will be applied on this platform using Time Resolved Amplified Cryptate Emission (TRACE) technology. This assay is based on a polyclonal antibody against calcitonin and a monoclonal antibody against katacalcin, which binds to the calcitonin and katacalcin sequence of the calcitonin prohormone. The test is considered a homogeneous immunoassay (sandwich principle) and is validated on serum and plasma (EDTA and heparin) matrix. The direct measuring range of the assay is from 0.02-50 ng/ml, with automated dilution extending the upper range to 1.000 ng/ml. The Functional Assay Sensitivity (FAS) is 0.06 ng/ml. Procedure time of the assay is very short at 19 minutes. The needed sample volume is limited to 50 micro litres. The Roche Elecsys BRAHMS procalcitonin assay equally uses an immunoassay based on a sandwich principle based on a polyclonal antibody against calcitonin and a monoclonal antibody against katacalcin, which binds to the calcitonin and katacalcin sequence of the calcitonin prohormone. The direct measuring range of the assay is from 0.02-100 ng/ml. The Functional Assay Sensitivity (FAS) is 0.06 ng/ml. Procedure time of the assay is also very short at 18 minutes. The needed sample volume is limited to 30 micro litres. The assay is validated on serum and plasma (EDTA and heparin) matrix. CRP and all other requested laboratory assays will be measured on the routine analyzers of the various sites and will be made available to the physician through the routine laboratory systems in place.

